**P** **ARENT OUTCOMES**					
Mental health	**Kessler 10 (K10**). A 10-item validated measure of adult psychological distress.^73^	Parent	●	●	●
Parenting stress	**Parenting Stress Index 4SF (PSI-4SF**). 36-item measure of parenting stress.^74^Provides a measure of total parenting stress and three subscales reflecting the major sources of parenting stress (parental distress, difficult child, parent–child dysfunctional interaction).	Parent	●	●	●
Quality of life	**Assessment of Quality of Life (AQoL4D**). 12-item measure of parent quality of life.^75^	Parent	●	●	●
**E** **CONOMIC** **OUTCOMES**					
Resource use	Family reported **service use** over preceding 3 months.	Parent	●	●	●
Health service utilisation	Permission to access both **Medicare and Pharmaceutical Benefits Scheme (PBS**) data for 3 months prior to baseline up until the last follow-up assessment.	Linkage	●	●	●

●Measure used at indicated time point.

3, 3 months; 6, 6 months; ASD, autism spectrum disorder; B, baseline; NIH, National Institutes of Health.

We have chosen the CSHQ as our primary outcome measure as this is a widely used and validated measure of behavioural sleep problems in children,^49^ and was used in our pilot *Sleeping Sound* ADHD-ASD study.^48^ It has been used to examine sleep behaviour in children with ASD and correlates highly with the objective measure of actigraphy.^57^ It contains 33 items and includes 8 subscales: Bedtime Resistance (eg, *Child falls asleep in own bed*), Sleep-Onset Delay (eg, *Child falls asleep in 20 min after going to bed*), Sleep Duration (eg, *Child sleeps the right amount*), Sleep Anxiety (eg, *Child needs parent in the room to fall asleep*), Night Waking (eg, *Child moves to someone else’s bed during the night*), Parasomnias (eg, *Child talks during sleep*), Sleep Disordered Breathing (eg, *Child snores loudly*) and Daytime Sleepiness (eg, *Child has difficulty getting out of bed in the morning*). A 3-point rating scale from 1=*rarely* to *3*=*usually* is applied to each item, indicating the sleep problem frequency during the past week. Some items are reverse coded and higher scores are indicative of more sleep problems. The measure has good internal consistency (α=0.78) and each subscale also has adequate internal consistency (α=0.93–0.56).^49^

Knowledge of participant group status will be limited to the project coordinator and study clinicians. If a family spontaneously reveals their intervention status to another team member, this is noted on the participant file. Given that it is impossible to maintain participant blinding in a trial of this nature, we have carefully chosen some outcome measures that can be assessed in a blinded fashion. For example, we will include a blinded teacher-reported measure of sleep, behavioural, social and motor functioning. We will not inform teachers of the child’s group status and will ask parents not to inform teachers. We will also include blinded objective child measures of executive and school-based functioning.

### Sample size

In our pilot study,^48^ we found a moderate to large effect of the intervention on sleep for total CSHQ score (standardised mean difference=0.7). However, since effect sizes from small studies may not be replicated in larger studies, we conservatively estimate a moderate standardised mean difference of 0.5 at 3-month and 6-month follow-up. Required sample size for this standardised mean difference was calculated using the equation n=2 (Zα+Z [1−β])^2^×SD^2^/d^2^, where Z_α_ was set at p<0.05 (two tailed), Z_1−β_ (power) was set at 0.80, d was set at 0.5 as per above and the SD for this standardised mean difference was set at 1. The resulting sample size estimate was then adjusted for the impacts of attrition (allowing for 20% loss to follow-up) and clustering (by individual and paediatrician). Clustering was handled with adjustments for design effect, assuming intraclass correlation (ICC)=0.08 for the within-child’s paediatrician clustering (average cluster size=4, SD=3) and ICC=0.20 for the within-person clustering to control for repeated measurement due to control of baseline scores (estimated based on unpublished pilot data).^58^ Allowing for 20% attrition over time and these forms of clustering, we will randomise a minimum of 234 children (117 in each group) to ensure sufficient power postintervention with our primary outcome time point at 3 months post-randomisation. Full calculations are available in the online supplementary file.

10.1136/bmjopen-2019-029767.supp2Supplementary data

Strategies have been put in place to encourage participant retention and the completion of the follow-ups. These include a four-step reminder process for completing follow-up assessments and a study newsletter to promote family engagement.

### Data analysis

Primary analysis will be intention-to-treat (within participant data included as per initial treatment group allocation, regardless of actual intervention received) and will compare outcomes of children in the TAU and intervention groups at the 3- and 6-month post-randomisation time points, though our primary endpoint is 3 months post-randomisation. Analysis of the primary outcome (ie, child sleep problems) and all secondary outcomes (child—teacher reported daytime sleepiness, sleep hygiene, emotional and behavioural problems, social communicative symptoms, cognitive performance, academic achievement, school attendance and quality of life; parent—parenting stress, mental health, quality of life and work attendance) will be carried out using linear mixed effects regression with results presented as mean differences (and 95% CIs). For each outcome, a single mixed-effects model will be fitted incorporating baseline, 3-month and 6-month data using random effects to allow for the repeated measures within an individual, and clustering of individuals within the child’s paediatrician. Separate parameters will be estimated for group differences at 3-month and 6-month postintervention; scores at baseline are added as a covariate. Differences in the outcomes of intervention and TAU groups will be assessed with linear mixed models, with individuals clustered within the child’s paediatrician and assessment times clustered within individuals. We will run an unadjusted model and compare this to an adjusted model, with the unadjusted model as our primary analysis, and adjusted results to evaluate robustness of these findings. The adjusted model will include the following as covariates: child gender, age, ASD symptom severity (measured using the Social Communications Questionnaire—current form,^53^ medication use (obtained from the Resource Use Questionnaire) and SES (measured according to the families residential postal code and using the index of relative socioeconomic disadvantage).^47 59^ The child’s paediatrician and individual participant will be modelled as random effects and the remaining variables will be handled as fixed effects. To account for missing data, the mixed models will be fitted using conditional maximum likelihood. As this approach makes an untestable assumption that data are missing at random, we will perform sensitivity analyses in the form of pattern mixture models to explore the effect of departure from this assumption. A per-protocol analysis will also be undertaken as a supplementary analysis. Significance will be tested at p<0.05 for the primary analysis, but adjustments for type I error inflation will be made for secondary outcomes by using the false discovery rate method.^60^

The number of siblings in the trial is expected to be low based on our prior work. Even if the proposed mixed effects model were able to run with family as a clustering factor despite low number of sibling pairs, there is still some concern about obtained parameter estimates.^61^ As such, alternative modelling approaches that can handle sparse data (such as generalised estimating equations) will be used as a sensitivity analysis to evaluate impact of clustering due to the presence of siblings on results obtained from our model without this correction.^61^

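### The primary mixed model names the baseline score both as a repeated measure and as a covariate; fitted literally, the 5% test at 3 months runs at about 9–12%.

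*Protocol article*

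**What the plan says.** The relevant text is in the Data analysis section of the protocol article.

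- Data in the model: "a single mixed-effects model will be fitted incorporating baseline, 3-month and 6-month data using random effects". The random effects are there to handle repeated measures within a child and clustering by paediatrician.
- Treatment terms and baseline: "Separate parameters will be estimated for group differences at 3-month and 6-month postintervention; scores at baseline are added as a covariate".
- Random effects: "The child’s paediatrician and individual participant will be modelled as random effects and the remaining variables will be handled as fixed effects". The nesting is described as "with individuals clustered within the child’s paediatrician and assessment times clustered within individuals".
- Status: the section compares an unadjusted and a covariate-adjusted model, "with the unadjusted model as our primary analysis".
- Error rate: "Significance will be tested at p<0.05 for the primary analysis". The Sample size section makes this two-sided.

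No sentence in the article takes the baseline row out of the response or limits baseline to one of the two roles.

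**The concern.** Baseline can properly enter a longitudinal model in either of two ways. It can be a predictor of the follow-up scores, or it can be the first of the repeated responses. Taken together, the two sentences do both.

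The baseline rows are then predicted by themselves, with two consequences. The common baseline slope is pulled above the true slope of follow-up on baseline. The baseline rows also leave residuals that are too small, and these are pooled with the follow-up residuals to estimate the variance components behind the 3-month standard error.

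Randomisation keeps the estimated group difference unbiased. What suffers is the standard error, the 95% CI and the p value of the primary comparison. The p values passed to the false discovery rate procedure are affected too, for the secondary outcomes that have a baseline score.

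**Working it through.** **1. The plan's own figure.** Inputs from the Sample size section: two-sided 5%, power 0.80, standardised difference 0.5, SD 1, paediatrician ICC 0.08 with mean cluster size 4, within-person ICC 0.20, 20% attrition.

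- Per arm before adjustment: 2 × (1.960 + 0.842)² / 0.5² = 62.8.
- Paediatrician design effect: 1 + (4 − 1) × 0.08 = 1.24.
- Within-person design effect with two measures: 1 + (2 − 1) × 0.20 = 1.20.
- 62.8 × 1.24 × 1.20 / 0.80 = 116.8, so 117 per arm and 234 in total, as stated.
- With three measures the last factor is 1 + (3 − 1) × 0.20 = 1.40, and 62.8 × 1.24 × 1.40 / 0.80 = 136.3, so 137 per arm, which does not match.

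**2. Size of the distortion by hand.** Assume unit variances and one common correlation r between all visits, and ignore the paediatrician level. With a random intercept, the baseline slope settles at β = (1 + 2r)/3 instead of r. The baseline row then has residual variance (1 − β)², and a follow-up row has 1 − 2βr + β². The model pools these over three rows.

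- r = 0.5: β = 0.667; baseline row 0.111; follow-up row 0.778; pooled (0.111 + 2 × 0.778)/3 = 0.556. Approximate ratio of model SE to true SD: √(0.556/0.778) = 0.85.
- r = 0.2: β = 0.467; rows 0.284 and 1.031; pooled 0.782; ratio 0.87.
- r = 0.7: β = 0.80; rows 0.04 and 0.52; pooled 0.36; ratio 0.83.

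The baseline residual is not negligible: 1 − β is 0.53 at r = 0.2 and 0.20 at r = 0.7. It is still small enough to shrink the pooled variance. The approximation ignores the remaining within-child covariance, so simulation is needed for the exact figure.

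**3. Simulation with no true effect.** 188 children (about 80% of 234), 47 paediatricians with 4 children each, paediatrician ICC 0.08, random intercepts for child and paediatrician, REML, test at 1.96, 1500 trials per row. Monte Carlo error is about 0.6 points at 5% and 0.8 at 10%. Correlations are baseline/3 months, baseline/6 months, 3/6 months.

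| Correlations | Literal model: type I error | Literal model: SE / true SD | Baseline as covariate only | Baseline as response only, common mean |
|---|---|---|---|---|
| 0.25, 0.25, 0.25 | 10.7% | 0.845 | 6.1% | 5.7% |
| 0.5, 0.5, 0.4 | 9.7% | 0.850 | 5.1% | 4.7% |
| 0.5, 0.5, 0.5 | 9.9% | 0.854 | 5.1% | 4.9% |
| 0.5, 0.5, 0.6 | 11.2% | 0.806 | 5.9% | 6.3% |
| 0.5, 0.5, 0.7 | 10.7% | 0.822 | 4.9% | 6.3% |
| 0.6, 0.6, 0.7 | 10.7% | 0.813 | 4.9% | 6.0% |
| 0.7, 0.7, 0.7 | 11.4% | 0.801 | 5.6% | 5.4% |
| 0.4, 0.4, 0.7 | 11.3% | 0.812 | 4.5% | 6.0% |

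In the first two rows the correlation between follow-ups after control for baseline is 0.20, the protocol's within-person ICC.

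**4. Sensitivity.**

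- No paediatrician level, equal correlations of 0.2, 0.4, 0.5, 0.6 and 0.7, 3000 trials each: 8.8%, 11.0%, 10.4%, 10.6% and 11.4%.
- Lowest literal-model result in any run: 7.4% (all correlations 0.2, no paediatrician level, 1000 trials).
- Highest: 13.1–14.0%, without the paediatrician level, when the two follow-ups correlate at 0.7 with each other but at 0.4–0.5 with baseline.
- Adding a group term at baseline to the literal model, in the setting of the table: still 9.3–10.7%.

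**5. Consistency.** A ratio of 0.86 implies a two-sided error of 2 × [1 − Φ(1.96 × 0.86)] = 9.2%, and a ratio of 0.80 implies 11.7%. A nominal 95% interval would then cover about 88–91%.

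**The case against.** The best reply is that the sponsor meant an ordinary analysis of the follow-up scores with baseline as covariate. Several things fit that. The text says only that baseline data are incorporated and never mentions an outcome vector. The following sentence states how baseline enters, as a covariate. Group parameters are named only at 3 and 6 months. The sample size reproduces with two repeated measures, not three. That last point is compatible with the covariate-only reading but does not prove it, because the Sample size section does not say which two measures it counts.

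The sentence also cannot be literal for every outcome. Table 3 shows WRAT and the NIH Toolbox at 6 months only, and the DBC without a 3-month visit.

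The size, too, depends on a correlation that the article does not report. If the effect were taken as a change-from-baseline contrast, the inflation would be smaller (about 4–9% in runs without the paediatrician level). The section, however, specifies group differences at each follow-up.

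These arguments make the fault conditional on the reading; they do not remove it. The article does not leave the point open for a later plan. It names the visits, random effects, treatment terms and covariate, and an analyst who follows that list fits the defective model. If covariate-only was meant, the wording contradicts the intent.

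**Conclusion.** The wording is defective and should be corrected before the primary analysis. Fitted literally, the model gives an unbiased 3-month difference with a standard error about 14–20% too small and a two-sided type I error of about 9–12% at a nominal 5%. This rests on an assumed baseline/follow-up correlation of 0.2–0.7 and on the stated random intercepts.

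Three stronger inferences are not supported. First, a reader might conclude that the trial's primary test is known to run at double its nominal level. The text also admits a covariate-only reading, under which the error is nominal. Second, a reader might extend the fault to every secondary outcome. It can reach only those with a baseline score, which excludes WRAT and the NIH Toolbox. Third, a reader might doubt the sample size on this ground. The 234 reproduces and is not affected.

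**What to change.** Give baseline one role, in one of two ways.

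- **(a)** The response is the 3- and 6-month scores only. Fixed effects are group, time, group×time and the baseline score.
- **(b)** The response is baseline, 3 and 6 months, with one common baseline mean for both arms, group differences at 3 and 6 months, and no baseline covariate.

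In either case keep the stated participant and paediatrician random effects and name the 3-month group difference as the primary contrast. If (a) was always intended, it is enough to say that baseline is a covariate only and is not among the responses. State separately how outcomes without a baseline score are handled.

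A baseline×time term and an unstructured within-person covariance are optional. The latter is worth considering under (b). In runs without the paediatrician level and with unequal correlations, (b) with random intercepts alone reached 6.4–8.9%, while (a) stayed at 4.7–5.0%.

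The cost is a sentence or two. The article reports that follow-up collection was still under way, and no further data or participants are needed. The downside is a confidence interval wider than the literal model would report.

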### Randomisation

The flow of participants from recruitment to follow-up assessments is displayed in figure 2. Participants are randomised to either the intervention or TAU groups by an independent research assistant once consent forms and baseline surveys have been completed. Treatment allocation is determined sequentially, according to a computer-generated block randomisation sequence with 1:1 ratio between groups, with blocks of randomly varying size (4, 6 and 8) developed by an independent statistician who is not involved in the project. The independent statistician will then upload this randomisation list into REDCap,^54^ a secure research database, to ensure allocation concealment. Given the relatively fewer diagnoses of ASD among girls,^55^ randomisation is stratified by gender to ensure equal representation of girls, boys and other genders (ie, transgender, intersex) in both study arms. Siblings are eligible to participate in the study provided they each meet all inclusion criteria. Families with siblings enrolled in the study are randomised in sequence based on the return of the primary parent baseline surveys, with all subsequent siblings allocated to the same treatment group. All families are sent a letter informing them of their group allocation and are not able to enrol further siblings once notified of group allocation. A study clinician then telephones intervention families to book the intervention sessions.

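### K10 and AQoL4D describe the parent, but the main model takes the child as the individual, so a parent with two enrolled siblings may be counted twice

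*Protocol article*

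**What the plan says.** All references are to the protocol article.

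- **Randomisation.** "Siblings are eligible to participate in the study provided they each meet all inclusion criteria". Later siblings go to the arm of the first. The order for sibling families follows the return of the primary parent's baseline surveys.
- **Recruitment: stage 2.** The survey is completed by the child's primary parent.
- **Measures, Table 3, parent outcomes.** The K10 is "A 10-item validated measure of adult psychological distress", and the AQoL4D measures the parent's own quality of life. Both are collected at baseline, 3 months and 6 months.
- **Data analysis.** The same mixed model serves the primary outcome and all secondary outcomes. Parent mental health, quality of life and work attendance are named among the latter. The model works by "using random effects to allow for the repeated measures within an individual, and clustering of individuals within the child’s paediatrician". There is no family or parent level.
- **Data analysis, closing paragraph on siblings.** Few siblings are expected, and no figure is given. A family level is left out because its estimates would be doubtful with few pairs. Methods such as GEE "will be used as a sensitivity analysis to evaluate impact of clustering due to the presence of siblings".

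**The concern.** For a child outcome such as the CSHQ, two siblings are two different subjects whose scores are correlated. For the K10 and AQoL4D, the subject is the parent. If a parent of two enrolled children has a score on each child's record, the model treats one adult as two individuals.

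The individual random effect links repeated measures within a child's record, not across siblings' records. Baseline adjustment does not help, because the two records would share nearly the same baseline as well. The only link left is a shared paediatrician, where there is one.

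Because siblings are always in the same arm, the error runs one way: standard errors for these outcomes come out too small, and parents with two enrolled children get double weight.

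**Working it through.** **The plan's own figure.** The Sample size section uses a two-tailed 5% level and 80% power, says "we conservatively estimate a moderate standardised mean difference of 0.5 at 3-month and 6-month follow-up", and adds that "the SD for this standardised mean difference was set at 1".

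- Per arm before inflation: 2 × (1.96 + 0.8416)² × 1² / 0.5² = 62.79
- Paediatrician design effect (ICC 0.08, mean cluster size 4): 1 + (4 − 1) × 0.08 = 1.24
- Within-person factor (ICC 0.20, read as 1 + 0.20): 1.20
- Attrition of 20%: divide by 0.80
- 62.79 × 1.24 × 1.20 / 0.80 = 116.8, so 117 per arm and 234 in total

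The stated 234 is reproduced. It was set for the CSHQ, a child outcome, so the parent-outcome question does not change it.

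**Size of the effect on a parent outcome.** Inputs:

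- p, the share of children enrolled as sibling pairs. The article says only that siblings will be few, so p is an assumption. The working range is 2% to 10%, with 20% as an extreme.
- ρ, the correlation between the two records of one parent. It is set to 1 (same person, same score), which is the worst case.
- r, the correlation the model already gives siblings: 0 with no shared paediatrician, or 0.08 (the planning ICC) with one.

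Among n children there are np/2 pairs, and each adds a covariance of 2ρσ² to the sum. The variance of a mean is therefore (σ²/n)(1 + pρ), while the model assumes (σ²/n)(1 + pr). Then:

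- D = (1 + pρ) / (1 + pr)
- Standard error too small by 1 − 1/√D
- True two-sided type I error = 2 × [1 − Φ(1.96/√D)]

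Example with p = 0.10 and r = 0: D = 1.10 and √D = 1.049. The standard error is 1 − 1/1.049 = 4.7% too small. The type I error is 2 × [1 − Φ(1.869)] = 6.2%.

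| p | Pairs among 234 | r = 0: D; SE too small by; type I error | r = 0.08: D; SE too small by; type I error |
|---|---|---|---|
| 2% | 2.3 | 1.020; 1.0%; 5.2% | 1.018; 0.9%; 5.2% |
| 5% | 5.9 | 1.050; 2.4%; 5.6% | 1.046; 2.2%; 5.5% |
| 10% | 11.7 | 1.100; 4.7%; 6.2% | 1.091; 4.3%; 6.1% |
| 20% | 23.4 | 1.200; 8.7%; 7.4% | 1.181; 8.0%; 7.1% |

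The paediatrician term absorbs little, because 0.08 is far below 1. If ρ were only 0.5, with r = 0.08, the type I error would be 5.1%, 5.2% and 5.5% at p = 2%, 5% and 10%.

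**Check by simulation.** A two-group comparison at one time point was simulated with 187 completers (234 × 0.80), identical scores within pairs and 20,000 replicates. The rejection rates were 4.9% at p = 0, 5.3% at 5%, 6.2% at 10% and 7.6% at 20%, in line with the formula.

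**The case against.** The strongest reply is that the plan already deals with siblings. It says openly that the main model does not correct for them, gives a reason, and plans a GEE-type analysis that is not limited to child outcomes. A GEE clustered on family with a robust variance would cope with any within-family correlation, including 1. This stands, so a reader who infers that sibling clustering was overlooked would be wrong. What remains is narrower. The main intervals for K10 and AQoL4D would still come from the uncorrected model, and the sparse-pairs argument does not justify that. Taking the parent as the unit requires no family variance component.

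Second, double entry is not stated. A reader might infer that the article prescribes entering one parent's score twice. It does not. The survey completed by each child's primary parent, and the reference to surveys in the plural for sibling families, point that way, but the second describes the order of randomisation. A data-set rule not shown here may already settle it, so the point has to stay conditional.

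Third, a reader might extend the point to work attendance and to productivity loss in the societal costing. The article does not support that. The Economic evaluation section says only that the Resource Use Questionnaire collects parent productivity. If it asks about work lost because of the index child, the answers differ between siblings and adding them is correct.

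Fourth, these secondary outcomes are judged under false discovery rate control, so 5.2–6.2% is not the error rate of the final decision rule. That is right. The figures describe the unadjusted test, whose p-values would enter that procedure.

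**Conclusion.** The point holds as a minor clarification, conditional on parent scores being entered once per enrolled child. In that case the main analysis of K10 and AQoL4D counts a parent of two enrolled children twice, with almost none of the correlation modelled. With identical scores and an assumed 2–10% of children in sibling pairs, the standard error is about 1–5% too small and the unadjusted type I error is about 5.2–6.2%. With fewer siblings, or scores that differ between surveys, the effect is smaller.

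It would be tempting to conclude that the trial's main result or its size is at risk. Neither is: the primary CSHQ outcome is specific to the child, and the 234 was derived for it. Parenting stress is also outside the point, because the PSI-4SF has subscales on the difficult child and the parent–child interaction that can differ between siblings.

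**What to change.** State in the analysis plan that, in the main analysis of K10 and AQoL4D, the parent is the individual, with one record per parent per time point. By default the record comes from the first-randomised child's survey, or from the sibling's survey if that one is missing. This removes both the double weight and the understated standard error. The alternative is to keep all records and use a family-robust variance. That corrects the standard error but leaves the double weight.

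Apply the same rule to work attendance and productivity loss only if the questionnaire asks about the parent's total lost work. If it asks about work lost because of the index child, leave these per child. Keep child-specific measures and the PSI-4SF per child, with the planned sensitivity analysis for siblings.

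The cost is a sentence or two and no new data. A few near-duplicate records drop out, about 2 to 12 of 234 at the assumed shares, with a very small loss of information where the two surveys differ. According to the Overall study design section, recruitment has closed but follow-up is still under way, so the rule can be set before analysis.

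### Gender stratifies the randomisation but is left out of the primary model: a small, conservative loss of precision if gender is prognostic, removable with one model term

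*Protocol article*

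**What the plan says.** Under Randomisation, allocation follows a "computer-generated block randomisation sequence with 1:1 ratio between groups", in blocks of 4, 6 or 8, and "randomisation is stratified by gender to ensure equal representation of girls, boys and other genders". Gender is the only stratification factor named.

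Under Data analysis, each outcome gets one linear mixed model. It has separate group differences at 3 and 6 months and random effects for the child's paediatrician and the individual, and "scores at baseline are added as a covariate". Two versions are planned, "with the unadjusted model as our primary analysis, and adjusted results to evaluate robustness of these findings". On the second version the article says: "The adjusted model will include the following as covariates: child gender, age, ASD symptom severity", followed by medication use and SES. Gender is not mentioned for the primary version. 'Unadjusted' therefore means without these five covariates; the baseline score is still in.

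**The concern.** Blocking within gender strata forces the arms to be nearly balanced on gender, so differences between genders contribute almost nothing to the sampling variation of the treatment contrast. A model without gender does not know this. It leaves the variation between genders in the residual and reports a standard error that is too large whenever gender predicts the outcome given baseline. The confidence interval is then wider than the design warrants and the test rejects too rarely under the null hypothesis.

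At stake is some precision on the primary outcome and on every secondary outcome analysed the same way. The planned power is close to 80% with little to spare, and the term that recovers this precision is already known for every child.

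**Working it through.** **Inputs from the article (Sample size).** Standardised difference d = 0.5, SD = 1, two-sided alpha 0.05, power 0.80, 20% attrition, paediatrician ICC 0.08 with mean cluster size 4, within-person ICC 0.20, total 234 (117 per arm).

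**Inputs assumed.** Share of girls p = 0.20 (0.30 as a variant). Gender difference δ, in outcome SDs given the baseline score, from 0 to 0.8. The article states neither.

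**Step 1: the plan's own figure.**
- n = 2(1.960 + 0.842)² × 1² / 0.5² = 62.79 per arm.
- Design effect = (1 + 3 × 0.08) × (1 + 1 × 0.20) = 1.24 × 1.20 = 1.488.
- 62.79 × 1.488 / 0.80 = 116.8, so 117 per arm and 234 in total. The stated figure reproduces.
- Effective size per arm = 117 × 0.80 / 1.488 = 62.9. Standardised effect λ = 0.5 / √(2/62.9) = 2.804. Power = Φ(2.804 − 1.960) = 80.1%.

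The formula takes no credit for gender.

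**Step 2: effect of omitting the stratifier.** Gender explains R² = p(1 − p)δ² of the residual variance. Under stratified allocation the true variance of the treatment difference is about (1 − R²) times what the model without gender reports. Hence:
- standard error overstated by a factor 1/√(1 − R²);
- actual alpha = 2[1 − Φ(1.96/√(1 − R²))];
- power without gender = Φ((λ − 1.96)/√(1 − R²));
- power with gender = Φ(λ/√(1 − R²) − 1.96).

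| p | δ | R² | SE overstated by | Actual alpha | Power without gender | Power with gender |
|---|---|---|---|---|---|---|
| any | 0 | 0 | 0% | 0.050 | 80.1% | 80.1% |
| 0.20 | 0.2 | 0.0064 | 0.3% | 0.0493 | 80.15% | 80.32% |
| 0.20 | 0.3 | 0.0144 | 0.7% | 0.0484 | 80.24% | 80.64% |
| 0.20 | 0.5 | 0.0400 | 2.1% | 0.0455 | 80.55% | 81.65% |
| 0.20 | 0.8 | 0.1024 | 5.6% | 0.0386 | 81.35% | 84.13% |
| 0.30 | 0.5 | 0.0525 | 2.7% | 0.0441 | 80.71% | 82.14% |

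Power forgone at p = 0.20: 80.32 − 80.15 = 0.17 points at δ = 0.2, and 81.65 − 80.55 = 1.10 points at δ = 0.5.

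**Step 3: check by simulation** (stratified blocks of 4, 6 and 8, 126 effective children, 20% girls, no treatment effect).
- δ = 0.5: the model without gender reported a mean SE of 0.178, against an empirical SE of about 0.175, and rejected in 4.4% of runs. With gender the reported SE was 0.174 and rejection 4.9%.
- δ = 0.8: rejection was 3.8% without gender and 4.9% with it.
- δ = 0.2: the two models were practically alike (5.2% and 5.3%). An effect that small is lost in simulation noise.

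**The case against.** The strongest reply is that nothing here is invalid. The error is in the cautious direction, so a positive primary result could not be overturned on this ground. The sample size took no credit for gender, so the 80% target is met without it. The point estimate already benefits from the stratified balance; only its reported standard error lags behind. All of this stands.

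Large effects also need strong assumptions. At 20% girls, R² = 5% requires δ = √(0.05/0.16) = 0.56 SD after conditioning on baseline, which is more than the treatment effect the trial is powered for. R² = 10% requires √(0.10/0.16) = 0.79 SD. The baseline score in the primary model should absorb much of any stable gender difference. This holds for the primary outcome, the Children's Sleep Habits Questionnaire. It does not hold for the Wide Range Achievement Test and the NIH Toolbox, which Table 3 schedules at 6 months only, so that they have no baseline score.

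A gender-adjusted analysis is already planned, and the article fixes in advance which model decides. A reader might still infer that the two models could fall on either side of p = 0.05 because of gender. The article does not support that attribution: the adjusted model adds four other covariates besides gender, and any of them could cause a disagreement. Nor does the adjusted model match the allocation exactly, since later siblings take the first sibling's arm. The article expects few siblings, so this matters little.

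**Conclusion.** The point holds as a minor one. The primary model omits the factor on which randomisation was stratified and, if gender is prognostic given baseline, reports a standard error that is slightly too large. With an assumed 20% girls and a gender difference of 0.2 to 0.5 SD, the overstatement is about 0.3% to 2%, actual alpha is about 0.049 to 0.046, and 0.2 to 1.1 points of power are forgone. With no gender effect there is no loss. These sizes rest on assumed values, because the article gives no figure for either quantity.

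A reader might go further and conclude that the primary test is invalid, the estimate biased or the trial underpowered. None of these follows: the estimate is unbiased, type I error stays at or below its nominal level, and 234 children still give the planned 80% power under the article's own assumptions.

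**What to change.** Add gender as a fixed effect to the primary model for every outcome, coded by the strata as actually randomised. The article names other genders as a category and describes no pooling, so set a rule before analysis for a very sparse level. For example, fit it as its own level unless it is too sparse to estimate, and otherwise combine it with a level named in advance. Keep age, SCQ score, medication and SES for the supportive adjusted model, so that the two models then differ only by covariates that the design does not call for.

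The cost is one model term (one or two degrees of freedom) using data already held for every child. The sample size and data collection do not change. The article reports 3- and 6-month collection as still under way, so at that point the change could be made before analysis.
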